**Discussion:**

We hypothesize that both intervention groups will show significant improvements compared to the control, with walking expected to yield greater gains in mental vitality and meditation to better enhance cognitive empowerment. Findings may support the implementation of community-based, non-pharmacological programs to promote active aging.

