### Sample size

The required sample size was calculated using G* Power software, based on the method described by Kazazi et al. [13]. Among the study objectives, the one requiring the largest sample was selected as the basis for estimation, specifically the evaluation of the intervention’s effect on cognitive empowerment in older adults. According to prior data, the mean (±standard deviation) of the mental status examination scores after the intervention was 28.3 ± 1.8 in the intervention group and 27.5 ± 2.1 in the control group. Using these values, the calculated effect size was 0.41. With a statistical power of 95% and an alpha level of 0.05, and assuming two repeated measurements after the intervention, the minimum required sample size was determined to be 58 participants. To account for a possible 20% attrition rate and a design effect of 1.6 due to cluster sampling, the final adjusted sample size was increased to 111 participants, resulting in 37 individuals per group.

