### Statistical methods

To assess the homogeneous distribution of confounding variables across the three groups before the intervention, the chi-square test was used for categorical variables, and one-way ANOVA was applied for continuous variables. All analyses will follow the intention-to-treat principle. Missing data (up to 14%) will be imputed using regression methods.

The primary analysis will test the superiority of the interventions on the primary outcome: change in cognitive empowerment score at week 8. To account for multiple comparisons, the significance level for the three pre-planned between-group comparisons (walking vs. control, meditation vs. control, walking vs. meditation) will be adjusted using the Bonferroni correction, resulting in a corrected alpha of 0.0167.

Changes in outcomes over time, between groups, and their interaction will be analyzed using the generalized estimating equation (GEE) model. Baseline individual and clinical variables showing significant between-group differences (e.g., age, marital status, physical activity) will be included as covariates to control for potential confounding. Analyses for secondary outcomes will be considered exploratory.

All analyses will be conducted using Stata version 17, with a two-tailed alpha level of 5% for tests not covered by the primary correction. Graphs will be generated using GraphPad Prism version 8.

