Tailored interventions, such as group walking and meditation, are designed to address the specific needs and preferences of older women, which can enhance participant engagement and satisfaction. Furthermore, the comprehensive data collection strategy, including pretest, posttest, and follow-up assessments, allows for a robust analysis of intervention effects over time. The implementation of blinding methods in the randomized allocation helps to reduce potential biases in participant assignment and outcome assessment, further strengthening the reliability of the results. Additionally, while the randomized block design aims to minimize selection bias and ensure balanced group allocation, the potential for study attrition exists, which could impact the study’s statistical power. To address this concern, regular follow-ups and personalized support mechanisms will be implemented to encourage participation and retention throughout the intervention period.

However, the study also has limitations. The sample size may limit the study’s statistical power, potentially affecting the ability to detect significant differences between groups, particularly if attrition occurs. Additionally, the 3-month follow-up period after the intervention may not be sufficient to assess the long-term effects of the interventions on the physical and mental health of participants.

Reliance on self-report questionnaires may introduce response bias, as participants may under- or overestimate their experiences or outcomes. While this study includes participants from diverse locations, the focus on older women may limit the applicability of the findings to other populations, such as older men or younger age groups. Furthermore, factors such as socio-economic status, preexisting health conditions, and social support systems may influence the results but may not be fully controlled, potentially affecting the validity of the findings.

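### The fixed Bonferroni level of 0.0167 for all three primary comparisons is valid, but a step-down rule with the same 5% family error would never reject less and would help the claim that both activities beat control

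*Protocol article*

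**What the plan says.** The Statistical methods section of the protocol article names three pre-planned comparisons of the week-8 change in cognitive empowerment: "walking vs. control, meditation vs. control, walking vs. meditation". Their level "will be adjusted using the Bonferroni correction, resulting in a corrected alpha of 0.0167". The same level applies to each comparison whatever the other two show, and no step-down, closed or hierarchical rule is named. Other tests are run "with a two-tailed alpha level of 5% for tests not covered by the primary correction".

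The abstract states the expected result for both arms: "We hypothesize that both intervention groups will show significant improvements compared to the control". The Hypothesis and Study design sections likewise aim at superiority of both activities over control.

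The Sample size section works "With a statistical power of 95% and an alpha level of 0.05", takes scores of "28.3 ± 1.8 in the intervention group and 27.5 ± 2.1 in the control group" and reports that "the calculated effect size was 0.41". It ends with 37 women per group, after allowing for 20% attrition and a design effect of 1.6. The Discussion concedes: "The sample size may limit the study’s statistical power, potentially affecting the ability to detect significant differences between groups".

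**The concern.** The three comparisons are all the pairwise contrasts of three arm means, so their null hypotheses are logically linked. If one equality is false, at most one of the other two can be true. Once the smallest p-value has passed 0.0167, holding the other two at 0.0167 is stricter than a 5% family error requires.

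An example shows what is at stake. Suppose walking beats control at p = 0.010 and meditation beats control at p = 0.030. Under the plan, meditation cannot be declared superior. Under Shaffer's step-down it can, at the same 5% family error and whatever the third p-value is. The extra strictness bears on the second rejection, and the hypothesis about both activities needs that second rejection.

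**Working it through.** **The plan's own figures.** 0.05/3 = 0.01667, which rounds to the stated 0.0167. The effect size is d = (28.3 − 27.5)/√((1.8² + 2.1²)/2) = 0.8/1.956 = 0.409, which agrees with the stated 0.41.

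**Rules compared** (thresholds for the ordered p-values, smallest first):
- Bonferroni: 0.0167 / 0.0167 / 0.0167
- Holm: 0.0167 / 0.025 / 0.05
- Shaffer, for all pairwise contrasts of three arms: 0.0167 / 0.05 / 0.05

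The two step-down rules stop at the first non-significant test.

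**Why the family error stays at 5%.**
- All three nulls true: a false claim requires the smallest p-value to fall below 0.0167, so the error is at most 3 × 0.0167 = 0.05.
- Exactly one null true: there is only one possible false rejection, and its level never exceeds 0.05.
- Exactly two nulls true: this cannot occur with three means, because two equalities imply the third.

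The first threshold is the same in all three rules and the later ones are never lower than 0.0167, so no Bonferroni rejection is lost.

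**Inputs for the size of the loss.**
- From the Sample size section: d = 0.41, 37 per arm, 20% attrition, design effect 1.6.
- Assumed: both activities have d = 0.41 over control, equal SDs, two-sided pooled-variance t-tests, and independent participants except in the design-effect row.
- The Primary outcome section defines a change from baseline. The variance of a change score relative to a single score is 2(1 − ρ). At an assumed correlation ρ = 0.5 this is 1, so there is no precision gain. The noncentrality is 0.41/√(2/37) = 1.76.
- Baseline adjustment, which the plan does not state, would give a factor of 1 − ρ² = 0.75 at ρ = 0.5.
- Attrition with the design effect leaves 37 × 0.8/1.6 = 18.5 effective women per arm.

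**Simulated results.**

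| Quantity | Bonferroni | Holm | Shaffer |
|---|---|---|---|
| Both beat control, change score, 37 per arm | 12.7% | 16.3% | 22.3% |
| Each active arm vs control, same setting | 25.7% | 27.5% | 30.6% |
| At least one rejection, same setting | 39% | 39% | 39% |
| Both beat control, baseline-adjusted, 37 per arm | 20% | 25% | 32% |
| Both beat control, 18.5 effective per arm | 4.3% | 5.9% | 9.0% |
| Family error, all arms equal | 4.4% | 4.4% | 4.4% |
| Error on the one true null, both activities strongly and equally effective | 1.7% | 5.0% | 5.0% |

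In the first row Bonferroni forgoes (16.3 − 12.7)/16.3 = 22% of Holm's chance and (22.3 − 12.7)/22.3 = 43% of Shaffer's. In 2,000,000 simulated trials per scenario, no case arose in which Bonferroni rejected and a step-down rule did not.

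**If power were as planned.** If each active-control comparison really had 95% power at 0.05, the joint chance would be 81.3%, 85.5% and 90.4%, a gain of 4 to 9 points.

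**The case against.** Bonferroni is a valid and prespecified choice. The family is named, limited to one primary outcome and correctly computed. A reader might infer that the correction is an error or leaves the family error uncontrolled. The documents do not support that: nothing in the section is misstated or contradictory.

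The plan also sets no joint success criterion. It lists three separate comparisons, and for a single active-control comparison the gain is only about 2 points (Holm) or 5 points (Shaffer). If success formally required both arms to beat control, testing both at 0.05 would need no correction at all. This limits how much weight the joint figure can carry, but does not remove the point. The abstract, Hypothesis and Study design sections all aim at both activities beating control, and that claim needs the second rejection.

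A reader might also infer that the multiplicity rule is why power is low, or that step-down testing would rescue the trial. Neither follows. At d = 0.41 and 37 per arm, one comparison has about 26% power at 0.0167 and only about 42% even at 0.05. The admission of limited power in the Discussion concerns sample size and attrition. With the protocol's own attrition and design effect, more than 90% of trials fail to show both activities superior under every rule. The 20%, 25% and 32% figures would make the gain look larger, but they rest on a baseline-adjusted analysis that the plan does not state.

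Finally, fixed Bonferroni keeps simple simultaneous intervals that match its decisions. That is a real, though modest, advantage.

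**Conclusion.** The point holds as one of efficiency, not validity. For the change-score analysis, the fixed rule costs about 4 points against Holm and 10 points against Shaffer in the chance of showing both activities superior. Allowing for attrition and the design effect, the cost is about 2 and 5 points.

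These sizes rest on d = 0.41 in both arms and an assumed correlation of 0.5. The 0.41 itself comes from mental status examination scores, not from the primary questionnaire. The direction does not depend on these assumptions, because the step-down rules can never reject less. The larger gain needs Shaffer's rule; Holm's is moderate. The improvement is cheap and worth making, but it is secondary to the sample size.

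**What to change.** In Statistical methods, before unblinding, replace the fixed 0.0167 with a step-down rule at a family-wise two-sided 0.05. Order the three p-values and test the smallest at 0.0167. If it is significant, test the other two in order, each at 0.05, stopping at the first that is not significant. Name the rule as Shaffer's procedure for all pairwise contrasts of three arms. Holm (0.0167/0.025/0.05) is the more familiar alternative, with a smaller gain; it would not rescue the p = 0.030 in the example unless the walking-meditation comparison also passed its own step first.

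The cost is one sentence, with no new participants, data or software. The drawback is that simple Bonferroni simultaneous confidence intervals will no longer agree exactly with the test decisions. The text should say so and state which intervals are reported beside the GEE estimates.

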### Sampling method

A two-stage cluster sampling method will be used to ensure adequate sample representation. Khafr County comprises nine comprehensive health centers, including three urban and six rural centers. Additionally, the rural centers will be affiliated with 27 health posts, each responsible for providing services to local families. In the first stage, each urban and rural comprehensive health center will be considered an independent cluster. Three centers (one urban and two rural) will be randomly selected. In the second stage, sampling will be conducted from the population covered by the selected centers. In each rural center, two affiliated health posts will be randomly selected. Then, eligible participants will be randomly chosen from the registries of these health posts and the selected urban center. To maintain equal representation, 50% of participants will be selected from urban areas and 50% from rural areas.

After enrollment, participants will be assigned to one of three groups, walking, meditation, or control, using block randomization. Each block will consist of 6 individuals, with a total of 20 blocks stratified by setting: 10 urban and 10 rural. Allocation concealment will be ensured using sealed envelopes, and responsibilities will be separated so that the person enrolling participants will be different from the one assigning them to groups. Participants will be placed in blocks based on registration order. Each block’s group codes will be enclosed in a sealed envelope. Upon registration of each set of six participants, the envelope will be opened, and codes will be written on separate cards. The randomization coordinator will then be contacted to determine each participant’s group based on the assigned code. This process will be repeated for all participants. A third party using the 2022 version of the Sealed Envelope online tool, independent of both the enrolling staff and the intervention investigator, will perform randomization. To prevent information exchange between groups, the walking and meditation sessions will be scheduled at different times and supervised directly by the researcher.

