### Outcomes

#### Primary outcome

The primary outcome is the change in Cognitive Empowerment score from baseline to the post-intervention assessment at week 8. To measure this variable, the Ability to Recognize Cognitive Changes questionnaire will be used. This questionnaire was designed and psychometrically evaluated by Tarighat et al. [14]. The questionnaire consisted of 25 questions that assessed older adults’ ability to recognize their own cognitive changes across 8 dimensions on a 3-point scale: physical strength (5 questions), self-esteem (5 questions), spirituality (2 questions), commitment (2 questions), role performance (4 questions), situation recognition (2 questions), self-management (3 questions), and self-assessment (2 questions). The total score ranged from 25 to 75. A score of 0 to 25 indicates that older adults’ ability to recognize cognitive changes is at an unfavorable level, 25 to 50 at a relatively favorable level, and a score above 50 at a favorable level. The questionnaire’s reliability and validity have been established, demonstrating satisfactory content and construct validity alongside a Cronbach’s alpha of 0.70.

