### Demographic information

Demographic information includes age, gender, occupation, level of education, retirement status, marital status, number of children, whether children are dependent on you in any way, whether you are dependent on children in any way, economic status, with whom you live, number of medications used, history of chronic diseases, co-occurring chronic diseases, uncorrected disabilities, history of hospitalization in the past year, physical activity level, and self-rated health (Additional File 1). The research design management plan (Table 2) and SPIRIT diagram (Fig. 3) are presented below.

**Table 2 Tab2:** Project management plan

Stage		Tasks	Timeline	Responsibilities
1	Drafting and planning	• Designing a research proposal • Obtaining ethical approvals • Registration in the Iranian Clinical Trials System	1 month	Researcher
2	Recruitment and selection of participants	• Informing health centers • Calling for elderly women • Assessing entry criteria	2 weeks	Researcher and colleagues
3	Data collection	• Administering questionnaires (pretest) • Starting interventions • Monitoring the intervention process	1 month	Researcher and research team
4	Implementation of interventions	• Holding walking and meditation sessions • Holding meaningful conversations	1 month (8 sessions)	Researcher and facilitators
5	Post-intervention data collection	• Administering questionnaires (posttest) • Following up and collecting follow-up data	2 weeks	Researcher and research team
6	Data analysis	• Analyzing the collected data • Preparing a report of the results	1 month	Researcher and analysts
7	Dissemination of results	• Writing an article for publication • Presenting the results at conferences	1 month	Researcher

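### Covariates for the primary model are chosen by baseline significance tests, which pick out chance imbalance and would almost never bring in the urban/rural stratum; the baseline score and setting should be prespecified instead.

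*Protocol article*

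**What the plan says.** All of the following is in the protocol article.

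- **Baseline tests** (Statistical methods): the three groups are compared before the intervention, where "the chi-square test was used for categorical variables, and one-way ANOVA was applied for continuous variables". No separate significance level is given. The general rule is a "two-tailed alpha level of 5% for tests not covered by the primary correction".
- **Covariate rule** (same section): "Baseline individual and clinical variables showing significant between-group differences (e.g., age, marital status, physical activity) will be included as covariates". The stated purpose is to control confounding. The variables in brackets are examples, and no covariate is fixed in advance.
- **Model** (same section): "Changes in outcomes over time, between groups, and their interaction will be analyzed using the generalized estimating equation (GEE) model". The section does not say whether the baseline score is one of the responses or an adjustment term.
- **Primary outcome** (Primary outcome): "The primary outcome is the change in Cognitive Empowerment score from baseline to the post-intervention assessment at week 8".
- **Multiplicity** (Statistical methods): three pairwise comparisons, "resulting in a corrected alpha of 0.0167".
- **Randomisation** (Sampling method): blocks of six, "with a total of 20 blocks stratified by setting: 10 urban and 10 rural". Setting is not mentioned in the Statistical methods section, nor in the list of baseline variables that begins "Demographic information includes age, gender, occupation, level of education, retirement status, marital status, number of children".

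**The concern.** Once allocation is random, a test of baseline differences between arms asks whether chance produced an imbalance, and the answer is already known. It does not show which variables predict the outcome, and only those make the treatment comparison more precise. The rule therefore lets chance settle the covariate list, and it is blind to the two variables with the strongest claim to be there.

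- **Baseline score of the same outcome.** This is usually the best single predictor of the week-8 score. It is used through the change score but is not named as a covariate.
- **Urban/rural setting.** Stratified blocks balance it across arms, so a test for imbalance will almost never select it.

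What is at stake is precision, and a primary model that cannot be written down before baseline data are seen. With 37 women per arm, the article's own Discussion accepts that the sample size may limit power.

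**Working it through.** **1. The plan's own figures.** Corrected alpha: 0.05 / 3 = 0.0167, as stated. Effect size from the Sample size section (28.3 ± 1.8 against 27.5 ± 2.1): 0.8 / √((1.8² + 2.1²)/2) = 0.409, as stated (0.41). Both are used below.

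**2. How often the rule fires by chance.** The Demographic information section lists 18 variables. Gender is constant in a trial of women, which leaves 17. The level is taken as 0.05 from the general rule.

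- Expected number flagged: 17 × 0.05 = 0.85. This does not need independence.
- Chance of at least one, if independent: 1 − 0.95^17 = 0.58.
- The items overlap (chronic diseases, co-occurring diseases and medications; occupation and retirement), which lowers this. If they behaved like 15 independent tests it would be 1 − 0.95^15 = 0.54; like 10, 0.40.

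**3. Whether the rule could select setting.** Complete blocks of six within each setting put equal numbers in each of the three arms. Only an incomplete block can unbalance a setting, and by at most two women between arms. A chi-square test of setting by arm will be close to zero.

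**4. Change score against baseline adjustment.** Take the same standard deviation (set to 1) at both visits, and correlation r between baseline and week 8. The variance of change is 2(1 − r). The variance after adjustment for baseline is 1 − r². The ratio is (1 − r²) / (2(1 − r)) = (1 + r)/2. The article gives no r, so a range is assumed. Power is by normal approximation, Φ(0.41 / (σ√(2/37)) − 2.394), where 2.394 is the two-sided critical value at 0.0167. It is before attrition and clustering.

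| r (assumed) | Change variance | Adjusted variance | Ratio | Extra participants a change analysis needs | Power, change | Power, adjusted |
|---|---|---|---|---|---|---|
| 0.3 | 1.40 | 0.91 | 0.65 | 54% | 18% | 29% |
| 0.5 | 1.00 | 0.75 | 0.75 | 33% | 26% | 36% |
| 0.7 | 0.60 | 0.51 | 0.85 | 18% | 45% | 53% |

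The extra participants are 1/ratio − 1.

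**5. What the selected covariates do.** This depends on the model.

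- If baseline is a GEE time point, with complete data and a full group-by-time structure, the week-8 interaction equals the difference in mean change. A covariate that is constant over time and entered as a main effect cancels, so estimate and standard error do not move. The rule then has no effect on the primary contrast.
- If the response is the change score, or the post-intervention scores alone, the estimate does depend on which variables were flagged.

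The second case, with change as the response, was simulated with 111 participants, 17 pure-noise candidates and a stratum explaining an assumed 5% of variance (2000 runs per scenario). At r = 0.5 and d = 0.41, power was 24.8% with the selected covariates, 25.4% for the plain change score, and 35.6% with baseline score and stratum prespecified. With no true effect, the selected-covariate analysis rejected in 1.6% to 1.9% of runs across the three values of r, against a nominal 1.67% (Monte Carlo standard error √(0.0167 × 0.9833 / 2000) = 0.3 percentage points).

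**6. Cost of omitting setting.** If setting explains a share R² of the analysed outcome, leaving it out inflates the standard error by 1/√(1 − R²): 1.01, 1.03, 1.05 and 1.12 for assumed R² of 0.02, 0.05, 0.10 and 0.20. The true level of the 0.0167 test then falls to 0.0156, 0.0140, 0.0116 and 0.0074. A setting effect that is constant over time cancels in a change analysis, and R² is then zero.

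**The case against.** The strongest reply is that only the selection rule is stated. The article does not say that the baseline score or setting is excluded, and a condensed article may leave the full model to an analysis plan. It also does not say that baseline is a GEE response. The Sample size section assumes two measurements after the intervention, which fits a model on post-intervention scores just as well. If that model already adjusts for baseline, the precision gain in step 4 is already in hand. This stands, and it makes the variance figures conditional. It does not rescue the rule, which is explicit.

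A reader might infer three stronger things that the document does not support.

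- **That the primary result depends on chance whatever the model.** It does not if baseline is a GEE time point: main-effect covariates then leave the week-8 contrast unchanged when data are complete.
- **That leaving out the stratum necessarily makes standard errors too large.** It does so only as far as setting predicts the analysed outcome.
- **That the false-positive rate is inflated.** The rule looks at baseline data and not at outcomes, the statistician is blind to group labels, and the simulated level stayed near nominal.

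One qualification concerns the word chance. Study design lists randomisation before baseline assessment in an open trial, whereas the recruitment text places the baseline interview directly after consent. If allocation is known when questionnaires are completed, self-reported baseline answers could differ for other reasons. That is a reason to make the order clear, since change scores and baseline adjustment both assume a baseline taken before allocation. It is no argument for selecting covariates by significance.

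**Conclusion.** The concern holds in a limited form. The plan has a stated, data-driven rule that selects covariates on chance imbalance, with 0.85 flags expected among 17 variables and up to about a 58% chance of at least one. By construction it would almost never select the stratification factor.

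The precision cost is conditional. If the GEE analyses change or treats baseline as a time point, adjustment for the baseline score would cut the variance of the contrast by 35%, 25% or 15% at an assumed r of 0.3, 0.5 or 0.7, and the gain vanishes as r approaches 1. The stratum is the smaller part: 1% to 12% on the standard error if setting explains 2% to 20% of the analysed outcome, and nothing if its effect is constant over time and change is analysed. The harm is a covariate list that is not fixed in advance and a probable loss of precision, not a shown error in the significance level. The change should be made, because it is free and the trial is small.

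**What to change.** - Delete the rule that admits covariates on significant baseline differences, and the baseline tests that feed it. Report baseline characteristics by arm descriptively.
- Prespecify the primary model as a GEE on the week-8 and 3-month scores, with group, time and group-by-time, adjusted for the baseline score of the same outcome and for urban/rural setting.
- Health centre may replace setting, but the two should not both be fixed effects. The Sampling method section selects one urban and two rural centres, so centre determines setting and the second term is redundant.
- Name the three week-8 group contrasts as the primary tests at 0.0167.

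The cost is about two sentences in the Statistical methods section and one or two degrees of freedom beyond the baseline score. All the variables are already collected. The Trial status section says that recruitment had not started at version 1.0; the change should be dated and made before group labels are released to the statistician. The exploratory aims on demographic and health characteristics are not affected.
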